### 2.6. Study Participants

The participants will be adults aged 18 years or older diagnosed with chronic HF who are classified as Stage C according to the ACCF/AHA HF staging system, and who have provided informed consent to participate in the study; the intervention group will receive in-person and phone-based care support program, and the control group will receive usual medical care and management at each healthcare facility.

### 2.7. Inclusion Criteria

Patients must have had one or more hospitalizations due to HF in the year preceding the index admission. Additionally, they must exhibit one or more of the following adherence-related issues:Living aloneDeterioration in familial support structuresMental health concerns, including depressionCognitive impairmentComplex medication regimens and instructionsExperiencing adverse drug reactions or side effectsInsufficient comprehension of medication regimenInadequate understanding of the disease process and prognosisChallenges in managing medication administration, weight monitoring, and fluid balanceMissing scheduled appointments (no-shows)

### 2.8. Exclusion Criteria

Patients are excluded who have impaired understanding or judgment due to factors which would make it difficult to obtain their consent to participate in the study.

## 3. Study Outcomes

### 3.1. Primary Outcomes

Self-care behavior improvement measured by EHFScBS. The Japanese version of the EHFScBS is a 12-item scale that uses a five-point response format, with lower total scores indicating better self-care behavior (range: 12–60); the questionnaire’s validity and the reliability of the Japanese version have been demonstrated [15].

### 3.2. Secondary Outcomes

Worsening HF, as evinced by the following:Incidence of readmission due to HF within 30 days, 3 months, 6 months, or 1 year after discharge;Duration of home care until readmission;Symptoms observed during unscheduled visits (prevention of symptom worsening through early visits);Changes in blood levels of BNP and NT-proBNP.

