Among these multidisciplinary team members, nurses are integral members, because nurse-led self-care interventions have been considered effective and cost-effective to improve cardiovascular disease, and offer numerous benefits, including a favorable perception of nurses as trusted healthcare professionals, a high quality of care delivery provided by these experts, a more frequent and consistent follow-up provided to patients, and the potential for lower healthcare expenditures [13,14]. Implementation of structured self-care interventions including early telephone support, especially by nurses, could effectively improve self-care behavior and prevent symptom deterioration among HF patients. Additionally, the intervention promotes early medical attention and shows preventive effects against worsening symptoms during unscheduled visits.

The aim of the study described in this protocol is to conduct a cluster RCT to compare the clinical effectiveness of early nurse-led structured telephone support intervention with the usual care. In addition to assessing cardiovascular outcomes, such as all-cause death and HF rehospitalization, the study will also evaluate the effectiveness of the interventions through self-care assessments, considering the mechanism of the intervention. Overall, this study could provide valuable evidence on the effectiveness of nurse-led telephone interventions in improving self-care behavior and outcomes for HF patients.

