### 2.5. Randomization and Blinding

Eligible facilities will be gathered through open solicitation. The joint research institutions will be selected based on discussions among and comprehensive review by the internal meetings of this association. We will assign the intervention group (facility) and the control group (facility) at a 1:1 ratio through stratified randomization according to the volume of potential patients. Patients from each facility who provide their consent will be included as intervention subjects. Since the study involves a behavioral intervention without a potential placebo counterpart, it will be impossible to blind both investigators and participants to group allocations. However, data collection research assistants will be trained on consistent administration of measures and awareness of biases.

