## 4. Interventions

The intervention will be conducted in healthcare facilities that provide inpatient and outpatient care for chronic HF. The intervention will be carried out by HF nurses or nurses with at least 3 years of experience in HF nursing. The intervention period is set for three months after discharge, with a focus on the first month as a period of intensive support (Figure 1).

On the third day after discharge, support is provided via phone to the patient and their family to confirm their living situation, medication adherence, and self-management status related to weight and blood pressure control. If the patient was discharged to a facility, information is gathered from the facility staff and nursing consultation and guidance is provided to the patient and staff. In-person support for approximately 30 min is provided at the first outpatient visit after discharge (usually about 2 weeks later). For one month after discharge, support is provided once a week via in-person or phone methods. Following the initial month where support is provided weekly, both in-person and phone support will be offered once a month for the next three months. Depending on the patient’s condition and the judgment of the nursing staff, additional support may be provided as needed.

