## 5. Control

During hospitalization, the usual medical care and discharge instructions according to the patient’s condition are provided, in the same manner as for the intervention group. In the outpatient setting, routine outpatient visits and care are also provided in each medical institution. The usual care is based on the concept of self-monitoring for HF patients and follows the disease-management program outlined within the heart failure guideline in Japan. Therefore, patient education during hospitalization is conducted appropriately, specifically including providing education to HF patients on self-monitoring their symptoms and other findings. However, regarding post-discharge care, even if the environment for structured nurse interventions is available, these are not implemented in the control group, in order to ensure a clear distinction between the intervention and usual care [19].

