In the intervention group, the same set of items as the baseline data, such as symptom control status, self-care behavior, self-reported symptoms and signs, and social circumstances will be collected at occurrence of readmission due to HF within 30 days or 3 months after discharge. The reason for readmission and duration of home care until readmission are collected. In addition, to capture the status of the intervention, the number of outpatient visits, including unscheduled visits, and the dates, times, and number of sessions by telephone and in-person are noted. If there are unscheduled teaching sessions, their content is also noted in the record. If the intervention has resulted in avoidance of hospitalization due to early visit or adjustment of oral medications, this should be reported.

In the control group, the same set of items as in the baseline data will be collected at 3 months after discharge. As with the intervention group, occurrence of readmission due to HF within 30 days or 3 months after discharge, and the reason for readmission and duration of home care until readmission are noted. Additionally, the number of outpatient visits (scheduled and unscheduled), and whether or not face-to-face medical guidance was provided are determined. If so, date, time, face-to-face time and content are collected.

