## 8. Statistical Method

The Japan Nursing Association will submit the data received from the intervention and control groups’ medical institutions to a contracted data analysis organization for analysis. The between-group comparison of the change in self-care behavior continuity and changes in BNP and NT-proBNP in the baseline values at discharge and changes after intervention (1 and 3 months later) will be performed. The Spearman rank correlation coefficient will be used to measure the relationship between the scores of cardiac functions and the EHFScBS. The Mann–Whitney U-test will be used to compare the scores of the EHFScBS between the two groups with respect to patient backgrounds. The McNemar test will be used to analyze the changes in the two groups’ readmission and symptom deterioration rates, with the corresponding t-test employed for frequency, relative risk, and absolute risk reduction for risk difference. The presence or absence of readmission and the time to readmission between the intervention and control groups will be analyzed by the Kaplan–Meier method and tested for significance using the log-rank test. The Cox proportional hazard model and propensity score analysis will be used to compare between-group differences. Multiple imputation techniques will be employed to handle missing data, ensuring robustness and reducing bias in the findings. In the above analysis for the comparison, covariate adjustment from the baseline patient characteristics will be applied to gain efficiency in the estimation for the treatment effect, when it is necessary.

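### Symptoms seen at unscheduled visits are listed as worsening HF, yet the intervention is meant to prompt early attendance, so comparing the arms on this item can mislead even when true worsening is equal

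*Protocol article*

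**What the plan says.** Section 3.2 introduces the secondary outcomes as "Worsening HF, as evinced by the following". The third item reads "Symptoms observed during unscheduled visits (prevention of symptom worsening through early visits". The Rationale gives the intended mechanism: "the intervention promotes early medical attention and shows preventive effects against worsening symptoms during unscheduled visits".

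The arms differ in how often a nurse could prompt a visit. Section 4 gives the intervention arm a telephone call on day 3, and then: "For one month after discharge, support is provided once a week via in-person or phone methods". Monthly support follows. For post-discharge care in the control arm, section 5 says that "even if the environment for structured nurse interventions is available, these are not implemented in the control group". On masking, section 2.5 states that "it will be impossible to blind both investigators and participants to group allocations".

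Section 6 counts unscheduled visits in both arms. It repeats the baseline item set at 3 months in the control arm. For the intervention arm, its text ties that item set to HF readmission within 30 days or 3 months. In the intervention-arm paragraph only, it also asks for a report: "If the intervention has resulted in avoidance of hospitalization due to early visit" or a change in oral medication. Section 8 names an analysis of the two groups' "readmission and symptom deterioration rates" and plans between-group comparisons of self-care and natriuretic peptides at 1 and 3 months.

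**The concern.** The item is conditional on an event after randomisation, the unscheduled visit, and the intervention is designed to influence that event. Randomisation balances the patients. It does not balance their chance of being observed once one arm is contacted weekly and encouraged to come in early.

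The outcome line also gives an early visit two opposite meanings. It sits under worsening HF, so a visit with symptoms is evidence of deterioration, while its parenthesis treats the early visit as the route by which deterioration is prevented. The article does not say which direction counts as benefit.

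At stake is the claim that the intervention prevents symptom worsening. A comparison on this item could point to harm or to benefit when true worsening is the same in both arms. Section 9 says the results are intended to support policy recommendations, so an uninterpretable secondary result could still be put to use.

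**Working it through.** The article gives no figure for this item, so there is none to reproduce. The check has a textual step and an illustration.

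**Step 1: does observation depend on the arm?**
- By its wording, section 3.2 observes the item only at an unscheduled visit.
- The Rationale says the intervention brings patients to medical attention early.
- Sections 4 and 5 give structured post-discharge contacts to one arm and withhold them from the other.

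If the intervention works as intended, the probability of a visit given worsening differs between arms. Bias needs nothing more than that.

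**Step 2: events counted per randomised patient.** All rates here are assumed. Observed rate = P(worsening) × P(unscheduled visit given worsening). True worsening is equal in the two arms.

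| True worsening, both arms | Attend, control v intervention | Observed, control v intervention | Spurious risk ratio |
|---|---|---|---|
| 20% | 50% v 60% | 0.20×0.50 = 10% v 0.20×0.60 = 12% | 1.20 |
| 20% | 50% v 75% | 10% v 0.20×0.75 = 15% | 1.50 |
| 30% | 40% v 50% | 0.30×0.40 = 12% v 0.30×0.50 = 15% | 1.25 |
| 30% | 40% v 60% | 12% v 0.30×0.60 = 18% | 1.50 |
| 30% | 40% v 80% | 12% v 0.30×0.80 = 24% | 2.00 |

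The spurious ratio is simply the ratio of the attendance probabilities. It does not depend on the true rate of worsening.

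With 105 patients per arm (section 2.3), a two-sided 5% test of two proportions and no allowance for clustering, the chance of a significant result against the intervention is:
- about 7% for 10% v 12%, and about 19% for 10% v 15%;
- about 9%, 23% and 62% for the three rows at 30%.

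With equal ascertainment, the chance in that direction would be 2.5%. With 40% attendance in control and 50–80% in intervention, and true worsening varied from 20% to 40%, the chance runs from about 7% to 78%.

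**Step 3: severity compared among attenders.** Assume 15% severe and 15% mild worsening in both arms. Severe cases attend at 80% in both arms, and mild cases at 20% in control v 60% in intervention.
- Control: severe 0.15×0.80 = 0.12; mild 0.15×0.20 = 0.03; severe share 0.12/0.15 = 80%.
- Intervention: severe 0.12; mild 0.15×0.60 = 0.09; severe share 0.12/0.21 = 57%.

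True severity is identical, but the intervention looks better. The bias has changed sign.

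**Step 4: do other symptom data repair this?** Only in part, on the text as it stands. Section 6 states a fixed 3-month collection for controls. The corresponding intervention-arm sentence is tied to HF readmission. Read literally, there is no common assessment time for intervention patients who are not readmitted.

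**The case against.** Several points on the other side are fair.

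*The analysis link.* A reader might infer that the symptom deterioration rates in section 8 are rates of symptoms at unscheduled visits. The article does not say so. Symptom items are also collected apart from such visits, so the rate could be a change from baseline. The limitation to attenders applies to this one item, not to all symptom data.

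*The direction.* A reader might infer that the comparison is biased in a known direction. The article does not say whether the item is a count, a proportion, a severity or a description, and that detail may sit in a fuller document. Defining it would settle which bias applies. It would not recover symptoms in patients who never attended, so the visit dependence stands.

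*Avoided hospitalisation.* A reader might treat this as a second biased outcome. It is not listed in section 3, section 8 names no analysis for it, and in section 6 it follows items recorded to describe how the intervention was delivered. What stands is narrower. It is an unblinded causal judgement recorded in one arm, so it cannot later serve as comparative evidence.

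*Missing 3-month data.* The caption of Figure 1 says the figure shows survey timing in both arms, and the figure is not available here. Section 8 plans 3-month comparisons. A common 3-month assessment may therefore already be intended, with section 6 poorly worded. That makes reconciling the text the appropriate request, not an allegation that the data are absent.

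*Mechanism.* Milder symptoms at presentation because patients come earlier is partly the effect the trial hopes for. That is a reason to describe it as a process result. It does not show that fewer patients worsened.

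**Conclusion.** The point holds in this form: symptoms seen at unscheduled visits should not be read as evidence of worsening HF in a comparison of the arms, because attendance is something the intervention is meant to change. The comparison can be biased with equal true worsening, and the sign depends on a summary measure that the article does not state.

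No size can be derived from the article. The spurious risk ratios of 1.2 to 2.0 in the working, and the 80% v 57% reversal among attenders, rest wholly on assumed worsening and attendance rates. The significance probabilities also ignore clustering. The structural conclusion needs only that attendance given worsening differs by arm.

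The reach is limited. This is one of four items in the secondary outcome list. The EHFScBS primary outcome, HF readmission, time to readmission and the natriuretic peptides are not defined by unscheduled visits. The change should be made, but the main comparison does not depend on it.

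**What to change.** 1. In section 3.2, take symptoms at unscheduled visits out of the worsening-HF list. Report the visits, and the symptoms seen at them, by arm as a process or utilisation measure. Visits are already counted in both arms.
2. Base any comparison of symptom worsening on the left-HF, right-HF and low-output symptom items already on the baseline sheet, collected 3 months after discharge in all patients of both arms. State in section 8 that the symptom deterioration rate comes from these data.
3. Reconcile section 6 so that the 3-month collection reads the same for both arms and agrees with section 8 and Figure 1.
4. State that the avoided-hospitalisation note describes delivery of the intervention and will not be used as comparative evidence.

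The cost is small. At most it is one added 3-month form for intervention patients who are not readmitted, and only a wording change if that form is already planned. The drawback is that a 3-month snapshot misses transient episodes that resolved earlier, and patients who died, so it should be read alongside HF readmission.

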## 4. Interventions

The intervention will be conducted in healthcare facilities that provide inpatient and outpatient care for chronic HF. The intervention will be carried out by HF nurses or nurses with at least 3 years of experience in HF nursing. The intervention period is set for three months after discharge, with a focus on the first month as a period of intensive support (Figure 1).

On the third day after discharge, support is provided via phone to the patient and their family to confirm their living situation, medication adherence, and self-management status related to weight and blood pressure control. If the patient was discharged to a facility, information is gathered from the facility staff and nursing consultation and guidance is provided to the patient and staff. In-person support for approximately 30 min is provided at the first outpatient visit after discharge (usually about 2 weeks later). For one month after discharge, support is provided once a week via in-person or phone methods. Following the initial month where support is provided weekly, both in-person and phone support will be offered once a month for the next three months. Depending on the patient’s condition and the judgment of the nursing staff, additional support may be provided as needed.

## 5. Control

During hospitalization, the usual medical care and discharge instructions according to the patient’s condition are provided, in the same manner as for the intervention group. In the outpatient setting, routine outpatient visits and care are also provided in each medical institution. The usual care is based on the concept of self-monitoring for HF patients and follows the disease-management program outlined within the heart failure guideline in Japan. Therefore, patient education during hospitalization is conducted appropriately, specifically including providing education to HF patients on self-monitoring their symptoms and other findings. However, regarding post-discharge care, even if the environment for structured nurse interventions is available, these are not implemented in the control group, in order to ensure a clear distinction between the intervention and usual care [19].

## 6. Data Collection

Baseline information will be collected prior to intervention (Figure 2). This includes age, gender, duration since initial HF diagnosis, HF stage according to NYHA (New York Heart Association) classification, ACC/AHA classification, and MAGIC (Meta-Analysis Global Group in Chronic HF) score. Test values include height, weight (variation), BMI, blood pressure, LVEF (left ventricular ejection fraction), BNP and NT-proBNP blood tests, and scores on the “EHFScBS” for self-care behavior. Exercise tolerance is assessed using the ADL and Frailty Index and Clinical Frailty Scale, and cognitive function is evaluated using HDS-R and MMSE. Physical findings include symptoms of left HF (shortness of breath, dyspnea, rapid breathing, nocturnal cough, and orthopnea), symptoms of right HF (edema, right hypochondrial pain, loss of appetite, abdominal bloating, discomfort in the epigastric region), and symptoms caused by low cardiac output (fatigue, weakness, altered consciousness, restlessness, and decreased memory). Depression is assessed using the PHQ-9 and information on treatment status is collected. The presence or absence of remote monitoring system implementation, cardiac rehabilitation, past hospitalization episodes, utilization of HF notebook, family structure (living alone, decreased family functioning), discharge destination (home or facility with or without a nurse and primary care provider), social support system, and introduction of visiting nursing are also collected. Additionally, qualitative measures to capture patient experiences and satisfaction with the intervention will be reported, including details on support content (conducted in-person or by phone, with specific support details recorded) and patient reactions (content of patient statements) will be collected.

In the intervention group, the same set of items as the baseline data, such as symptom control status, self-care behavior, self-reported symptoms and signs, and social circumstances will be collected at occurrence of readmission due to HF within 30 days or 3 months after discharge. The reason for readmission and duration of home care until readmission are collected. In addition, to capture the status of the intervention, the number of outpatient visits, including unscheduled visits, and the dates, times, and number of sessions by telephone and in-person are noted. If there are unscheduled teaching sessions, their content is also noted in the record. If the intervention has resulted in avoidance of hospitalization due to early visit or adjustment of oral medications, this should be reported.

In the control group, the same set of items as in the baseline data will be collected at 3 months after discharge. As with the intervention group, occurrence of readmission due to HF within 30 days or 3 months after discharge, and the reason for readmission and duration of home care until readmission are noted. Additionally, the number of outpatient visits (scheduled and unscheduled), and whether or not face-to-face medical guidance was provided are determined. If so, date, time, face-to-face time and content are collected.

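### Section 6 sets different follow-up rules by arm for the primary-outcome EHFScBS, and neither rule supplies the 1- and 3-month comparison planned in Section 8

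*Protocol article*

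**What the plan says.** - **Primary outcome.** Section 3.1 of the protocol article defines it as "Self-care behavior improvement measured by EHFScBS" and gives no time point there.
- **Baseline set.** Section 6 places "scores on the “EHFScBS” for self-care behavior" among the items recorded before the intervention.
- **Intervention-arm follow-up (Section 6).** "In the intervention group, the same set of items as the baseline data, such as symptom control status, self-care behavior, self-reported symptoms and signs", together with social circumstances, "will be collected at occurrence of readmission due to HF within 30 days or 3 months after discharge".
- **Control-arm follow-up (Section 6).** "In the control group, the same set of items as in the baseline data will be collected at 3 months after discharge". Readmission is then listed as a separate item: "As with the intervention group, occurrence of readmission due to HF within 30 days or 3 months after discharge".
- **Analysis (Section 8).** A between-group comparison of self-care behaviour, BNP and NT-proBNP from the discharge baseline, where "changes after intervention (1 and 3 months later) will be performed".
- **Figure 1.** Its legend says that it shows when questionnaires are given in both groups. The figure itself was not available to this review.

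**The concern.** The rule for repeating the primary measure should be the same in both arms and should not depend on what happens after randomisation. As worded, the control rule is a calendar date for everyone and the intervention rule is an event. An intervention patient who stays out of hospital has no stated follow-up EHFScBS.

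Two things are at stake. First, sites cannot tell from Section 6 how to produce the data that Section 8 needs. Local researchers and nurses collect the data at up to 40 facilities, so the wording of the schedule matters. Second, if the sentence were followed literally, the comparison would set readmitted intervention patients, scored at the time of readmission, against all controls scored at 3 months. Readmission is plausibly linked to poor self-care, so this would probably count against the intervention. A score that was never collected cannot be recovered at the analysis stage.

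**Working it through.** **1. The two sections side by side.**

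| Needed by Section 8 | Intervention arm, Section 6 | Control arm, Section 6 |
|---|---|---|
| EHFScBS at baseline | yes | yes |
| EHFScBS at 1 month | not listed as a fixed collection | not listed |
| EHFScBS at 3 months | only on HF readmission | yes, fixed |

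Of the four follow-up cells, Section 6 fills one.

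**2. How the intervention sentence parses.** It could mean either (a) at a readmission that falls within 30 days or within 3 months, or (b) at a readmission within 30 days, or else at 3 months. The control paragraph repeats the wording about 30 days or 3 months, expressly as with the intervention group, and there the whole phrase qualifies readmission. Section 3.2 also uses a list of time windows to define readmission. Reading (a) is therefore the natural one. Under (b) a conflict would still remain, because there is no 1-month control collection and some intervention patients could be scored at readmission rather than at 3 months.

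**3. The plan's own sample size.** Inputs from Section 2.3: difference 4, SD 8.5, power 80%, dropout 30%, 105 per arm. Two-sided alpha 0.05 is assumed because none is stated.

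- n per arm = 2 × (1.960 + 0.842)² × 8.5² / 4² = 70.9, so 71.
- With dropout: 71 / 0.70 = 101.4, so 102 per arm and 204 in total. This is within 3% of 210, without any inflation for the ICC.
- Scores expected if both arms are measured: 105 × 0.70 = 73.5 per arm. SE = 8.5 × √(2/73.5) = 1.40, and power is about 81% before clustering.

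**4. The literal reading only.** The article gives no 3-month readmission rate, so 10–30% is assumed. Intervention scores = 105 × rate; control scores = 105 × 0.70 ≈ 74. SE = 8.5 × √(1/n₁ + 1/n₀), with a two-sample t-test for 4 units and no clustering.

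| Assumed readmission | Intervention scores | Control scores | SE | Power |
|---|---|---|---|---|
| 10% | 10 | 74 | 2.86 | 28% |
| 20% | 21 | 74 | 2.10 | 47% |
| 30% | 32 | 74 | 1.80 | 60% |

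The 30% dropout is a one-year figure and is applied here only to controls. With all 105 controls scored, the same calculation gives 29%, 50% and 64%, so this choice matters little.

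**5. Selection, on the literal reading only.** Suppose that the intervention has no effect and that readmitted patients score d SD worse than the others. All controls are measured, and a fraction r of them are readmitted too. The spurious difference is then (1 − r) × d × 8.5. With d assumed to be 0.2 to 0.5 and r 10–30%:

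- smallest: 0.70 × 0.2 × 8.5 = 1.2 units;
- largest: 0.90 × 0.5 × 8.5 = 3.8 units.

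Both are against the intervention, and the target difference is 4 units.

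**The case against.** The strongest reply is that nobody planned to measure only readmitted intervention patients. Section 8 compares change at two fixed times in both groups, Section 2.3 counts 105 patients in each arm, and the Figure 1 legend refers to questionnaire timing in both groups. On this view the fault is one badly worded sentence, and parse (b) above is open. This largely stands as a statement of intent, and it limits what can be claimed. It does not remove the conflict: Section 6 states two different rules, and neither gives the 1- and 3-month data.

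A reader might infer several stronger points that the documents do not support:

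- *That the trial will compare intervention failures with all controls.* This follows only from the literal reading, and Section 8 points the other way.
- *That the text rules out any common schedule in Figure 1.* The figure has not been seen and may show one. If so, it and Section 6 disagree and need aligning.
- *That no 1-month data will exist.* Section 8 names a 1-month change. What can be said is that Section 6 does not list its collection.
- *That two time points create uncontrolled multiplicity.* Naming the primary time and handling multiplicity are commonly left to the SAP, which is not shown.

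It could also be said that the SAP, the full protocol or the planned multiple imputation will settle the matter. A full protocol may well hold a clear schedule, but this article does not merely leave the schedule out: it gives one that differs by arm. On the literal reading imputation would not help, because no intervention patient who avoided readmission would have an observed follow-up score to inform the model.

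**Conclusion.** The point holds as an internal contradiction about the primary outcome. Section 6 ties the repeat EHFScBS to HF readmission in one arm and to a fixed 3 months in the other, and Section 8 needs common times that this schedule does not provide. That conclusion rests on the text alone, and confidence in it is high.

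The numerical consequences are conditional. They apply only if Section 6 is followed literally, and they depend on an assumed readmission rate, an assumed gap in self-care scores between readmitted and other patients, and an assumed two-sided alpha of 0.05. On those terms power for 4 units is roughly 28–60% before clustering, against about 81% with both arms measured, and the selection bias is about 1.2–3.8 units. Selection is the larger problem, since more patients would not cure it. If fixed surveys in both arms were intended and are carried out, neither loss arises and only the wording needs repair. The repair should be made in either case, because sites cannot make up a missed assessment later.

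**What to change.** - Amend Section 6 so that every patient in both arms completes the EHFScBS, and BNP/NT-proBNP where planned, at the same fixed times after discharge regardless of readmission. Include 3 months, the only fixed time now given for controls.
- Either add a 1-month collection in both arms or delete the 1-month comparison from Section 8.
- Keep the at-readmission record as an additional form in both arms; it should not replace the scheduled score.
- Check that Figure 1 shows the same schedule.
- When confirming the primary time point, reconcile the two descriptions of the intervention period in Section 4. One sets it at three months after discharge; the other describes a first month of weekly support and then monthly support for the next three months (1 + 3 = 4 months). It has to be clear whether support is still running at the 3-month assessment.

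The cost is a short amendment and one scheduled questionnaire per intervention patient, at a nurse contact that already exists. If the 1-month comparison is kept, a 1-month questionnaire is added in both arms. Sample size and treatment do not change.
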